## Abstract

**Background::**

The reproductive dilemma faced by men has always been the focus of the whole society. Idiopathic asthenozoospermia (AZS), as one of the common causes of male infertility, lack of specific treatment. Traditional Chinese medicine has shown potential benefits in the management of male infertility. Yishentongluo decoction (YSTL) is a representative Chinese herbal formula; however, there is still no rigorous clinical trial supporting its application. Therefore, we designed a randomized controlled trial to evaluate the efficacy and safety of YSTL for patients with idiopathic AZS and explain the possible action mechanisms of YSTL in improving sperm motility.

**Methods::**

In this randomized controlled study, a total of 160 eligible patients will be assigned to YSTL group or the Levocarnitine oral solution group in a 1:1 ratio. The treatment period will be 12 weeks and the follow-up period will last 4 weeks. The primary outcome will be the the progressive (motility), sperm rate (%). Secondary outcomes will include the progressive (motility) + non-progressive (motility) sperm rate(%), total effective sperm count, inner mitochondrial membrane potential (MMP) in spermatozoa, and spouse pregnancy rate (%). Safety outcomes will cover electrocardiogram , blood tests (including blood routine test, hepatic function, and renal function), urine routine test, and stool routine test. The semen parameters, sperm MMP test, and all the safety outcomes will be performed at the baseline, 4th, 8th and 12th week. The pregnancy outcome will be evaluated at 4 weeks after treatment.

**Discussion::**

This study will provide initial evidence regarding the efficacy and safety of YSTL in the treatment of idiopathic AZS with kidney deficiency and blood stasis pattern. In addition, potential mechanisms of YSTL in improving sperm motility will be explored based on sperm MMP test.

**Trial registration::**

Chinese Clinical Trials Register identifier, ChiCTR2000033290, registered on 26 May 2020.

## Introduction

1

Infertility is defined by the World Health Organization (WHO) as “the inability of a sexually active, non-contracepting couple to achieve pregnancy after 12months,”^[1]^ and it affects around 10% to 15% of couples all over the world.^[2]^ Male infertility, which is mainly associated with disorders in sperm such as low sperm count, poor sperm quality, or both, accounts for up to 50% of all infertility cases.^[3]^ Among them, decreased motility (asthenozoospermia, AZS) which is characterized by reduced spermatozoa forward motility (progressive motility < 32%),^[4]^ is one of the most frequent types of male infertility, and affects approximately 40% of all cases.^[5]^ Idiopathic asthenozoospermia was defined when the etiology was unknown. For decades, despite greater understanding of male infertility in recent years, idiopathic sperm abnormalities still account for about 30 percent of male infertility.^[6]^ Male infertility has a seriously negative impact on a man's physical, psychological, emotional well-being, especially family harmony, or even social relationships.^[7]^ Being a destructive and complicated disorder, male infertility attracting more and more public attention.

Male reproduction is a complex process, the most critical factor for male fertility is sperm motility, and any failures in sperm production, maturity, storage, or expulsion will lead to infertility finally.^[8]^ Asthenozoospermia can be a consequence of genital tract infection, abnormal hormone levels, varicocele, systemic diseases, environmental factors, or be the result of changes that have not yet been recognized at the molecular level.^[9–15]^ Recently, mitochondrial dysfunction reported in AZS men came to attention, several studies reported this dysfunction is related to idiopathic asthenozoospermia, since sperm motility is regulated by intrinsic factors, and requires an appropriate supply of adenosine triphosphate.^[16–18]^ For adenosine triphosphate synthesis, these gradients are generated by electron transfer maintained by the inner mitochondrial layer. Then energy storage in mitochondria is related to proton concentration and electric potential gradient in cell membrane. The energy state of mitochondria is described by mitochondrial membrane potential (MMP), which regulates intact functional mitochondria and is significantly correlated with the motility of sperm.^[19]^ Thus, we said the functional competence of the sperm can be evaluated by measuring the inner MMP in spermatozoa.^[20]^ It has been observed that highly progressive motility sperms do have higher MMP as compared to infertile males with impaired motility, and they are usually morphologically normal and can undergo acrosome reaction invariably at the same time.^[21,22]^ Therefore, analyse the function of mitochondria may provide a way to distinguish sperm motility and MMP can be considered as a potential regulator and indicator of sperm motility.^[8]^

Due to unknown etiology and complex pathogenesis, there are no specific therapies to effectively treat the idiopathic asthenozoospermia infertility, and a number of drugs are empirically managed using in the clinic.^[23]^ Some studies of antioxidants have tended to show that semen parameters may benefit from supplements of carnitine,^[24]^ vitamin E,^[25]^ Selenium,^[26]^ or N-acetylcysteine.^[27]^ However, the therapeutic potential of antioxidant remains debated, since limited by sample size.^[28]^ In recent years, L-Carnitine (LC) has attracted extensive attention in treating male infertility. LC which is mainly of exogenous origin not synthesized is an essential substance in the process of fatty acid oxidation, and plays an important role in the production and transport of energy in cells.^[29]^ In the study of Lenzi and collaborators, an interesting aspect has been found: there is a high concentration of carnitine in the male reproductive tract, particularly in the epididymis, representing its key role in energy metabolism and sperm maturation.^[30]^ Given this finding, it is now known that the accumulation of LC in ejaculation may be a marker of epididymal function.^[28]^ LC has been used as a treatment approach in patients with idiopathic asthenozoospermia, just mainly based on the crucial role of it in energetic metabolism and its concentration in epididymis.^[31]^ Some controlled and uncontrolled studies suggest the potentially positive effects of LC and its acyl derivatives in the treatment of some forms of oligoasthenoteratozoospermia.^[32,33]^ Then, recent clinical studies confirmed LC has been successful in treating men with asthenospermia.^[34]^

However, some treatments including LC are sometimes inefficient, costly, or related to side effects, about half of patients want to seek more alternative therapies such as Traditional Chinese medicine (TCM) to cure AZS.^[35,36]^ TCM has been used for hundreds of years in clinical practice to treat male infertility.^[37]^ In the theory of TCM, the kidney is the place to store kidney essence, which plays an important role in reproduction. Most experts believe that idiopathic AZS is closely associated with the dysfunction of the viscera, especially the disorder of the kidney.^[38]^ Several studies have revealed the active components of herbal medicine that nourish kidney-essence, support blood circulation in the reproductive system, and control testosterone secretion.^[39]^ They have been shown to significantly improve sperm motility in animal studies.^[40]^ And also shown positive effects in the enhancement of the parameters of sperm in men with infertility.^[13,41]^ Some small-sample clinical trials have confirmed the efficacy of Yishentongluo decoction (YSTL) as complementary therapy for idiopathic asthenospermia.^[42]^ Our previous study suggested that YSTL significantly improved sperm quality and sperm deoxyribonucleic acid integrity in patients with varicocele-associated asthenospermia combined with minimally invasive surgery.^[43]^ However, the present clinical study has the limitations of the methodology and sample size, and sufficient data on YSTL as complementary therapy compared with western drugs in idiopathic AZS are lacking. Thus, we aimed to design an randomized controlled trial to evaluate the efficacy and safety of YSTL in idiopathic AZS, and to explore the possible mechanism of it.

## Methods and analysis

2

### Design

2.1

A 12-weeks, single-center, assessor-blinded, randomized controlled trial is currently being performed. YSTL will be compared with Levocarnitine Oral Solution to evaluate the efficacy and safety of YSTL for patients with idiopathic AZS. The trial will be conducted in the Department of reproductive medicine, Henan Province Hospital of TCM. All participants will be required to provide written informed consent prior to entering the trial. The study schedule is detailed in Table 1. The flowchart of the trial is shown in Figure 1. The Standard Protocol Items: Recommendations for Interventional Trials checklist is provided as Additional file 1.

**Table 1 T1:**
[figure not shown]
Data collection points.

**Figure 1 F1:**
[figure not shown]
Trial flow chart.

### Ethic approval

2.2

The research protocol is performed in accordance with the principles of the Declaration of Helsinkii^[44]^ and has been approved by The Ethics Review Board of Henan Province Hospital of TCM (approval no. 2020-1120-2) and followed up the whole process. We registered the study on the Chinese Clinical Trial Registry (Registration No. ChiCTR2000033290).

### Participants

2.3

A total of 160 male patients with idiopathic AZS infertility will be enrolled in this study after their informed consents are obtained. We will post the printed recruitment posters in the hospital or release recruitment information on the hospital social media (QQ, WeChat, Weibo) to recruit participants. All participants should meet the diagnostic criteria of idiopathic AZS infertility and TCM pattern differentiation criteria of Kidney deficiency and Blood stasis. If they meet the study criteria, they will be invited to the Department of reproductive medicine, Henan Province Hospital of TCM to undergo the study. Eligible participants will be randomized at a 1:1 ratio to the YSTL group or the Levocarnitine Oral Solution (LOS) group. The course of treatment will last 12 weeks. The pregnancy of the wife will be followed up at 4 weeks after treatment.

#### Diagnostic criteria

2.3.1

Diagnostic criteria of idiopathic AZS infertility will be based on the WHO laboratory manual for the examination and processing of human semen, 5th ed, in 2010.^[4]^ To be specific, the following five criteria should all be met:

(1)the inability of a sexually active, non-contracepting couple to achieve pregnancy after 12months, due to the reason of the man;(2)two or more semen examinations (abstinence time for 3–7 days each time) of male suggested asthenozoospermia, AZS: progressive (motility) (PR) < 32%, or PR + non-progressive (motility) (NP) < 40%;(3)sperm concentration > 15 × 10^6^/mL;(4)proportion of normal sperm ≥ 4%; and(5)no obvious causative factors were found.

The TCM pattern differentiation criteria of Kidney deficiency and Blood stasis will refer to the Guiding Principles of New Herbs Research^[45]^ and the Guidelines for Diagnosis and Treatment of Male Infertility with Integrated Traditional Chinese and Western Medicine (Trial Edition).^[46]^ The standards of Kidney deficiency and Blood stasis were separated into major symptoms and secondary symptoms. Major symptoms: Couples of childbearing age who have lived together for more than one year, have regular sexual life, not taken any contraceptive measures, and the woman cannot become pregnant due to the man's reasons. Secondary symptoms:

(1)soreness and weakness of waist and knees;(2)dizziness and tinnitus;(3)dark tongue body with ecchymosis or petechia;(4)thick and tortuous sublingual veins; and(5)a deep and weak pulse, or a deep and unsmooth pulse.

Patients were considered to have Kidney deficiency and Blood stasis if they met all of the major symptoms and two secondary symptoms such as a and c, or a and d, or b and c, or b and d, and met the pulse manifestation.

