### Sample size

2.4

Sample size was estimated based on the primary study results. Our previous pre-experiment have shown that the effective rate (*P*_1_) of the YSTL group (treatment group) is 79%, and the effective rate (*P*_2_) of the LOS group (control group) is 54%. The the following formula was used to estimate sample size: 

with a 5% significance level (*α*= 0.05, two-sided) and 90% power (*β*= 0.1), the final sample size has been set at a total of 160 patients (80 in each group), assuming a 15% dropout rate.

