### Primary outcome

4.1

The primary outcome in this trial is PR sperm rate (%) at baseline and the 4th, 8th, and 12th week after randomization.

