### Secondary outcomes

4.2

The secondary outcomes will include:

(1)semen parameters including PR+NP sperm rate (%), and total effective sperm count;(2)the inner MMP in spermatozoa; and(3)spouse pregnancy rate (%).

The semen parameters and sperm MMP test will be performed at the baseline, 4th, 8th and 12th week after randomization. The pregnancy outcome will be evaluated at 4 weeks after treatment.

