### Statistical analysis

4.5

Statistical Product and Service Solutions (SPSS21.0, International Business Machines Corp., Armonk, NY) software will be performed using for statistical analysis of data by professionals who will be blinded to the whole trial process. Analysis of the efficacy and safety will be based on the principle of intention-to-treat that all random participants will be analyzed. The missing value will be handled by the method of multiple imputations. Data will be presented as mean with standard deviation, median with range, or number with percentage, and different data types will be analyzed by appropriate methods. A repeated-measures multifactorial analysis will be used to analyze value changes of PR sperm rate, PR+NP sperm rate, total effective sperm count, and inner MMP in spermatozoa (See Table 1). The rest of the secondary outcomes will compare the different spouse pregnancy outcomes. Safety outcomes will be compared with the incidence of adverse events in two groups using the *χ*^2^ test. All the statistical tests will be conducted by bilateral difference tests, and if a *P* value is less than 0.05, the data difference will be considered statistically significant.

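### As most naturally read, the analysis takes PR change from one baseline occasion and leaves the qualifying semen examinations unused, which costs precision but causes no bias

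*Protocol article*

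**What the plan says.** Entry (Protocol article, 2.3.1) rests on "two or more semen examinations", each after 3 to 7 days of abstinence and each pointing to asthenozoospermia, meaning PR below 32% or PR+NP below 40%. The Participants section (2.3) applies this to everyone: "All participants should meet the diagnostic criteria of idiopathic AZS infertility".

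The outcome is set in 4.1: "The primary outcome in this trial is PR sperm rate (%) at baseline and the 4th, 8th, and 12th week after randomization". Section 4.2 repeats the schedule for the other semen measures: "The semen parameters and sperm MMP test will be performed at the baseline, 4th, 8th and 12th week after randomization".

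The analysis in 4.5 reads: "A repeated-measures multifactorial analysis will be used to analyze value changes of PR sperm rate", together with PR+NP, total effective sperm count and mitochondrial membrane potential.

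The article does not say how many ejaculates make up the baseline, or whether the baseline is one of the qualifying samples or a new one. It does not say whether baseline is subtracted, entered as a level of the time factor or used as a covariate. It gives no laboratory or time window for the qualifying examinations, and no purpose for them beyond eligibility.

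**The concern.** PR varies from one ejaculate to the next within the same man. If the treatment comparison is a change from one sample, that sample's full within-man noise is carried into the contrast. The same holds if baseline is one level of the repeated factor and the test is group by time, because the week-12 versus baseline contrast is then the difference in mean change.

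Two inexpensive sources of precision would be lost. The first is using pre-randomisation PR as a covariate instead of subtracting it. The second is making that covariate more reliable with readings that eligibility already requires. Both use data from before randomisation only, so neither can bias the comparison between groups. What is at stake is the width of the interval for the primary comparison. No PR variance was used to size the trial, so nothing in the sample size section shows how wide that interval will be.

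**Working it through.** **The plan's own figure.** The Sample size section (2.4) gives effective rates of 79% and 54%, two-sided α 0.05, 90% power and 15% dropout. With unpooled variance, n = (1.960 + 1.282)² × (0.79×0.21 + 0.54×0.46) / 0.25² = 10.507 × 0.4143 / 0.0625 = 69.65 per group. Multiplied by 1.15 this is 80.1, so 80 per group and 160 in total. (Dividing by 0.85 instead gives 81.9.) The figure of 160 is reproduced, although the formula is not legible in the text and the variant cannot be confirmed. It rests on a binary rate and contains no PR variance, so it neither supports nor contradicts the point.

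**Formulas.** Let ρ be the within-man reliability, m the number of pre-randomisation readings and r the number of post-baseline readings, with equal variances and correlations. The treatment-effect variance is proportional to:

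- change from baseline: (1+(r−1)ρ)/r + (1+(m−1)ρ)/m − 2ρ
- baseline as covariate: (1+(r−1)ρ)/r − mρ²/(1+(m−1)ρ)

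The documents do not give ρ. The range 0.4 to 0.8 is an assumption.

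**Week 12 alone (r = 1), before allowing for selection**

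| Quantity | ρ = 0.4 | ρ = 0.8 |
|---|---|---|
| Change, one baseline: 2(1−ρ) | 1.200 | 0.400 |
| Covariate, one reading: 1−ρ² | 0.840 | 0.360 |
| Covariate, two readings: 1−2ρ²/(1+ρ) | 0.771 | 0.289 |
| Covariate, three readings: 1−3ρ²/(1+2ρ) | 0.733 | 0.262 |
| Cut: covariate instead of change | 30% | 10% |
| Further cut: two readings instead of one | 8.2% | 19.8% |
| Further cut: three readings instead of one | 12.7% | 27.4% |

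**Allowing for selection.** Men admitted for low values vary less between themselves, which changes these figures. Simulated men had a true mean PR of 22 to 28, total SD 9 before selection, ρ of 0.4 to 0.8, and were kept only if both screening values were below 32%. All of these inputs are assumptions except the 32% limit. Cuts in week-12 variance:

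- One separate baseline as covariate instead of a change score: about 14% (ρ = 0.8) to 35% (ρ = 0.4).
- Mean of three readings instead of one, both as covariates: a further 7% (ρ = 0.4) to 24% (ρ = 0.8).
- If the baseline is itself one of two qualifying samples, their mean instead of one: about 5% to 17%.

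Repeating the simulation moves the ends of these ranges by about one percentage point.

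**Scale.** Variance cuts of 7% and 24% correspond at N = 160 to 160/0.93 − 160 ≈ 12 and 160/0.76 − 160 ≈ 51 extra patients.

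**Mean of the three visits (r = 3)**, closer to the planned model. Without selection, three readings instead of one as covariate cut the variance by 24.2% (ρ = 0.4: 0.440 to 0.333) to 43.4% (ρ = 0.8: 0.227 to 0.128). With the selection above, the cut is 14% to 39%.

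**Adding versus replacing.** Under a wider set of assumed PR means and SDs (25/8, 32/12, 40/15), averaging two screening values with a separate baseline cut the three-visit variance by 9% to 38%. Replacing the baseline with the two screening values changed it by anything from a 1.5% loss to a 25% gain. The qualifying readings should therefore be added to the baseline sample, not substituted for it.

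**The case against.** The strongest objection is that this is a condensed article. How a baseline is derived and which covariates enter a model are commonly left to a fuller document, and nothing here is contradictory or invalid. That stands, and it limits the point to an improvement in efficiency.

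Four stronger readings are tempting but not supported:

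- **That the plan states a single-value baseline.** It names a baseline occasion, not a number of ejaculates. Value changes could also mean change over time across visits. The single-value reading is an inference, though the natural one.
- **That every man brings usable extra readings.** Each man must have had at least two examinations, but their laboratory and date are not given. Section 2.3 describes recruitment by poster and social media, with men invited to the department if they meet the criteria, so tests done elsewhere are possible. A man may also qualify on PR+NP instead of PR.
- **That the whole gain over a change score comes from the qualifying examinations.** The two steps together give about 35% to 39%. Roughly 40% to 88% of that comes from covariate adjustment with one baseline reading and needs no extra data.
- **That the primary analysis should move to week 12 alone.** That is a separate decision, and an argument about baseline precision does not justify it.

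A reader might also suspect bias from selecting on low values. Regression to the mean would exaggerate change within each group, but it affects both randomised groups alike and does not bias their comparison.

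**Conclusion.** The point holds as a minor, nearly free gain in precision. It has two separable parts. Covariate adjustment for baseline PR is available whatever the status of the qualifying tests. Averaging in the qualifying readings adds to it only where those readings are comparable with the baseline sample.

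The sizes rest on assumed values of SD and reliability, on readings that are interchangeable, and on both screening PR values being below 32%. Tests that are distant in time, done in another laboratory or missing for some men would reduce the averaging gain. The direction holds at every correlation examined, provided the qualifying readings are added to the baseline sample. The validity of the randomised comparison is not in question.

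**What to change.** In 4.5, keep the repeated-measures analysis of weeks 4, 8 and 12, and enter pre-randomisation PR as a covariate instead of as a repeated level or a subtracted value.

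In 4.1 or 4.5, define that covariate. Where qualifying examinations were done in the trial laboratory within a fixed window before randomisation, record them in the case record form and use their mean together with the baseline sample. Otherwise use the baseline sample alone. State whether the baseline sample may itself be one of the qualifying examinations. Apply the same rule to PR+NP, and settle it before unblinding.

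The cost is a sentence or two of text and one or two extra data fields, with no new tests or visits. The downside is that men will contribute unequal numbers of readings, so the covariate will be more reliable for some than for others.

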#### Inclusion criteria

2.3.2

Participants who meet all of the following conditions will be included. The inclusion criteria are as follows:

(1)males, aged between 23 and 48 years;(2)confirmed the diagnosis of male infertility and idiopathic AZS;(3)confirmed the TCM pattern differentiation criteria of Kidney deficiency and Blood stasis;(4)with normal sexual function, regular sexual life (the frequency of sexual life is required to be no less than 1 time/week); and(5)willing to join this research and sign an informed consent form.

